**Methods/Design:**

A prospective, longitudinal study will be used for this study. A total of 150 older critically ill patients in the ICU will participate (ICU group). Pain, anxiety, agitation, morbidity, mortality, use of the health care system, and health-related quality of life will be measured at 3 intervals after a baseline assessment. Baseline measurements will be taken 48 hours after ICU admission and one week thereafter. Follow-up measurements will take place 6 months and 12 months after discharge from the ICU. To be able to interpret trends in scores on outcome variables in the ICU group, a comparison group of 150 participants, matched by age and gender, recruited from the Swiss population, will be interviewed at the same intervals as the ICU group.

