### Participants and Setting

The study will be conducted in the interdisciplinary ICU of a Swiss university hospital, where approximately 4000 patients with surgical procedures, illnesses, and trauma are treated each year, as well as at 12 follow-up clinics. From this ICU, 150 older critically ill patients (age 65 years and older) will be recruited, to be followed until 1 year after discharge from the hospital (the ICU group). A sample of 100 patients will be needed, based on a power analysis; with a 95% confidence interval for an estimated prevalence of pain between 0.30-0.50 and a total of 0.20, a sample size of 81-96 is needed. In order to ensure a large enough sample, and to counteract the potential loss of participants through mortality, relocation, attrition, or other problems, an additional 50 participants will be recruited (150 total). In order to be able to interpret trends in scores in the ICU group for the outcome variables *pain, anxiety*, *agitation, HRQOL*, *use of the health care system *(readmissions, GP visits, rehabilitation, length of hospital stay), *medication use, living situation*, and *survival*, we decided to collect similar data in a comparison group. Participants of the comparison group are a convenience sample of older people from the Swiss population, who have not been admitted to an ICU for the last 15 years. Through matching of age and gender, an attempt is made to increase the comparability of the groups at baseline.

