## Measurements

### Background data

Demographic data include age, gender and marital status. Furthermore, health-related data including Activities of Daily Living (ADL) and co-morbidities will be collected at baseline for all participants. The severity of the patient's condition will be determined using the Acute Physiology and Chronic Health Evaluation (APACHE II) and the Simplified Acute Physiology Score (SAPS II) [27]. The performance of ADL will be measured using items querying the need for assistance with daily activities (home health care, home food delivery, residence in a retirement home or nursing home) and various quality-of-life dimensions such as physical function, physical role function, vitality and social role function (Short Form 36 Health Survey [SF-36]). A scale developed for this study will be used to assess the need for assistance with daily activities (completely dependent; needs support by caregivers and special medical equipment; needs caregivers; independent with medical equipment; completely independent). Co-morbidities will be measured using the International Classification of Diseases (ICD), Version 10 [28].

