### Data Analysis

The statistical analysis will be performed using the R Project for Statistical Computing. Descriptive statistical analyses (mean, median, interquartile range) will be used to describe and characterize the data. To indicate the strength and direction of relationships between variables, Spearman's rank correlation coefficient for ordinal data and Pearson's product-moment coefficient will be conducted, depending on measurement levels and data dispersion. The Mann-Whitney U Test will be used for continuous data when comparing groups, and random effects models will be used for the longitudinal data. Attrition (i.e., missing data) during the follow-up will be reported.

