## Discussion

This article presents the design of a prospective longitudinal study investigating the associations between admission to the ICU and pain, anxiety, agitation, health-related quality of life, and use of the health care system in later life. Previous longitudinal studies have examined ICU patients' health-related quality of life [4,7-9] or traumatic memories of postoperative treatment [2,5]. The present study specifically assesses situations involving pain, anxiety and agitation in older patients, as well as their consequences. These symptoms can influence the long-term outcomes of older critically ill patients. The study will be conducted over a period of two years. Data on health-related quality of life are time dependent and related to the life situation of the participant. Changes that take place during the follow-ups, such as modifications in therapy or accidents, were integrated into the analysis, based on the various measurement techniques. The instruments used for the study represent a limitation.

Various studies have attempted to explain ICU stay-related variables by using identical generic instruments to compare critically ill patients' health-related quality of life with that of comparison groups from the general population [4,9,41,42].

Apparently, illness-specific influences on health-related quality of life are not identified by these generic instruments. Various studies assessed HR-QOL with a variety of instruments [19,43] In addition, the effort required for older people to fill out multiple questionnaires is not negligible. Some studies on critically ill patients have questioned the patients' families regarding their health-related quality of life [44,45]. However, due to the subjective nature of quality of life, the current study uses only interview and questionnaire data provided by the patients themselves, in order to more accurately describe the patients' own perception of their ICU stay. Until now, little research has focused on the short- and long-term consequences of pain, anxiety, and agitation in older patients, including the effect on the patients' use of the health care system. Because inadequate pain assessment and management may needlessly increase hospital readmissions and the use of the health care system, this topic should be of broad interest. This study will provide the first data on the situation in Switzerland.

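### The only test named for comparing groups is an unadjusted Mann-Whitney U test, so for questions 1 and 3 prior ill health could be reported as an effect of the ICU stay

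*Protocol article*

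**What the plan says.** Under Study Aims, questions 1 and 3 ask in causal terms whether a stay in intensive care changes later pain, anxiety, agitation and health-related quality of life, after discharge and at 6 and 12 months.

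The reference for these questions is described under Participants and Setting: "Participants of the comparison group are a convenience sample of older people from the Swiss population". A history of recent intensive care rules a person out of that group, which is limited to those "who have not been admitted to an ICU for the last 15 years". On comparability the same section says: "Through matching of age and gender, an attempt is made to increase the comparability of the groups at baseline". The Abstract gives the size as "a comparison group of 150 participants, matched by age and gender, recruited from the Swiss population". Whether matching is in individual pairs or by frequency is not stated.

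The Data Analysis section gives the methods in one sentence: "The Mann-Whitney U Test will be used for continuous data when comparing groups, and random effects models will be used for the longitudinal data". It names no covariates and does not say which of the two methods answers questions 1 and 3.

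Under Background data, "Activities of Daily Living (ADL) and co-morbidities will be collected at baseline for all participants". Data Analysis gives these variables no role. Under Procedure, the ICU group is also asked, one week after discharge, to recall its quality of life and symptoms before admission. No such recall is described for the comparison group.

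The Discussion adds: "Changes that take place during the follow-ups, such as modifications in therapy or accidents, were integrated into the analysis". It does not say how. The same section describes the purpose of the study as investigating associations.

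**The concern.** The two groups differ by design in more than the ICU stay. One consists of people ill enough to need at least 48 hours of intensive care. The other consists of conveniently available older people who have had no ICU admission for 15 years, a restriction that the inclusion criteria do not place on the ICU group's earlier history. Age and gender are the only factors on which the groups are matched.

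The method named for comparing groups cannot separate the ICU stay from prior morbidity. An analyst who follows the sentence literally would report a rank-test p-value for, say, SF-36 scores at 12 months and read it as the answer to a question about the effect of the ICU stay. This is more than missing detail, because the document names a specific method for this purpose and that method cannot adjust. Recruiting more participants does not help: a larger sample makes a biased contrast more likely to reach significance.

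**Working it through.** **1. The plan's own figure.** Inputs from Participants and Setting: 95% confidence, pain prevalence 0.30 to 0.50, total interval width 0.20 (half-width 0.10).

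n = 1.96² × p(1 − p) / 0.10²

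- p = 0.30: 3.8416 × 0.21 / 0.01 = 80.67, i.e. 81.
- p = 0.50: 3.8416 × 0.25 / 0.01 = 96.04, i.e. 96.

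The stated 81 to 96 reproduces. It is rounded up to 100, and 50 are added for losses. The calculation concerns the precision of one prevalence, not a group contrast. The documents give no between-group effect, SD or within-pair correlation, so steps 3 and 4 use assumed inputs.

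**2. What the group comparison controls.**

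| Source of difference | Handled by design? | Handled by Mann-Whitney? |
|---|---|---|
| Age, gender | Yes, by matching | No |
| Co-morbidity before admission | Partly, by the exclusion criteria | No |
| ICU stay in the past 15 years | Excluded in the comparison group only | No |
| Selection into a convenience sample | No | No |

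**3. Illustration of confounding.** Assume no true ICU effect, a residual prior-health difference of δ SD, n analysable per group, a two-sided 5% level and a normal approximation.

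SE = √(2/n), which is 0.1414 for n = 100 and 0.1155 for n = 150.

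Rejection probability = Φ(δ/SE − 1.96) + Φ(−δ/SE − 1.96)

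Worked case, δ = 0.2 and n = 100: 0.2/0.1414 = 1.414, so Φ(−0.546) + Φ(−3.374) = 0.293.

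| δ (SD, assumed) | 100 per group | 150 per group |
|---|---|---|
| 0 | 5.0% | 5.0% |
| 0.1 | 10.9% | 13.9% |
| 0.2 | 29.3% | 41.0% |
| 0.3 | 56.4% | 73.8% |
| 0.5 | 94.2% | 99.1% |

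One way to arrive at such a δ: a co-morbidity present in 60% of one group and 30% of the other, and worth 0.5 SD, gives (0.60 − 0.30) × 0.5 = 0.15 SD. At 100 per group, 0.15/0.1414 = 1.061 and the rejection rate is about 19%. The prevalences and the 0.5 SD are assumptions too.

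**4. Does ignoring the matching matter?** Suppose matching was in individual pairs with within-pair correlation ρ (assumed). The unpaired test then has true size 2 × [1 − Φ(1.96/√(1 − ρ))]. Power is shown for an effect that has 80% power at ρ = 0.

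| ρ | Size, unpaired | Power, unpaired | Power, paired | Loss (points) |
|---|---|---|---|---|
| 0.05 | 4.4% | 80.6% | 82.0% | 1.4 |
| 0.10 | 3.9% | 81.3% | 84.0% | 2.7 |
| 0.20 | 2.8% | 82.7% | 87.9% | 5.2 |
| 0.30 | 1.9% | 84.3% | 91.8% | 7.5 |

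Ignoring pairs would make the test conservative at a modest cost in power. It would not produce false positives.

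**The case against.** The strongest reply is that the same sentence plans random effects models for the longitudinal data. Questions 1 and 3 concern repeated measurements, so their answers may well come from those models, which can carry covariates. Nothing says that the models are unadjusted, and a journal article may leave the covariate list to an analysis plan. Collecting co-morbidities in everyone is consistent with an intention to adjust. This stands in part. A reader might infer that the whole analysis is unadjusted, and the document does not support that. But it does give group comparison to a test that cannot adjust, and it does not say that the models take precedence for questions 1 and 3.

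Second, the exclusion criteria are stated for participants in general and remove dementia, psychotic illness and potentially terminal lung disease, heart disease and cancer. The ICU group also supplies a recalled pre-admission state. Both narrow the problem. Neither removes it: the exclusions leave other morbidity untouched, and the recall is retrospective, described for the ICU group only and given no analytic role.

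Third, the illustrated rejection rates would apply to any unadjusted observational comparison. That is right; they show sensitivity and do not estimate the bias in this study.

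Two stronger readings are tempting. One is that an unpaired test wastes the matching. Individual pairs are never mentioned, the balance in age and gender remains in any case, and step 4 shows a small cost even if pairs exist. The other is that the Discussion's sentence on changes during follow-up means adjustment for consequences of the ICU stay. The sentence does not say that these changes are covariates. Medication and health care use are outcomes of the study, so reporting them is an equally natural reading.

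**Conclusion.** The concern holds in limited form. As written, the method assigned to comparing groups on continuous outcomes cannot separate the ICU stay from prior ill health, and the comparison group was not assembled in a way that makes this unnecessary. For questions 1 and 3, which are worded as effects, a difference due to earlier morbidity could be reported as due to the ICU stay.

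The size is unknown from the documents. On assumed residual imbalances of 0.1 to 0.3 SD with no true effect, rejections run at about 11% to 56% with 100 per group and 14% to 74% with 150. These figures rest on a normal approximation to a difference in means and on equal numbers analysed per group.

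The finding does not extend to the random effects models, whose covariates are simply not described. It makes no claim of lost efficiency from matching. Over-adjustment for follow-up events is a concern only if those events are in fact entered as covariates. The stated sample-size figures are unaffected.

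**What to change.** In Data Analysis, state that:

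- the group contrasts for questions 1 and 3 come from the random effects model already planned, with group, visit and group × visit;
- the model is adjusted for age, sex and co-morbidities present before the ICU admission (before enrolment in the comparison group);
- a matched-set effect is added only if matching was in individual pairs, and the type of matching is stated;
- events and therapy changes after the ICU stay are not adjusted for in the main contrast, and the sentence in the Discussion is clarified accordingly;
- Mann-Whitney results are descriptive;
- conclusions on questions 1 and 3 are worded as associations, as the Discussion already does. Adjustment for recorded co-morbidity will not remove all confounding.

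Baseline ADL should not be added as a routine adjuster. In the ICU group, Table 2 places baseline one week after ICU discharge, and ADL is partly measured with SF-36 dimensions, so it may already reflect the ICU stay.

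Cost: a few sentences, plus some work in the ICU group to separate co-morbidities present before admission from later ones, since Table 2 records morbidity at the post-discharge visit from records and questionnaire. No new recruitment is needed.

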## Discussion

This article presents the design of a prospective longitudinal study investigating the associations between admission to the ICU and pain, anxiety, agitation, health-related quality of life, and use of the health care system in later life. Previous longitudinal studies have examined ICU patients' health-related quality of life [4,7-9] or traumatic memories of postoperative treatment [2,5]. The present study specifically assesses situations involving pain, anxiety and agitation in older patients, as well as their consequences. These symptoms can influence the long-term outcomes of older critically ill patients. The study will be conducted over a period of two years. Data on health-related quality of life are time dependent and related to the life situation of the participant. Changes that take place during the follow-ups, such as modifications in therapy or accidents, were integrated into the analysis, based on the various measurement techniques. The instruments used for the study represent a limitation.

Various studies have attempted to explain ICU stay-related variables by using identical generic instruments to compare critically ill patients' health-related quality of life with that of comparison groups from the general population [4,9,41,42].

Apparently, illness-specific influences on health-related quality of life are not identified by these generic instruments. Various studies assessed HR-QOL with a variety of instruments [19,43] In addition, the effort required for older people to fill out multiple questionnaires is not negligible. Some studies on critically ill patients have questioned the patients' families regarding their health-related quality of life [44,45]. However, due to the subjective nature of quality of life, the current study uses only interview and questionnaire data provided by the patients themselves, in order to more accurately describe the patients' own perception of their ICU stay. Until now, little research has focused on the short- and long-term consequences of pain, anxiety, and agitation in older patients, including the effect on the patients' use of the health care system. Because inadequate pain assessment and management may needlessly increase hospital readmissions and the use of the health care system, this topic should be of broad interest. This study will provide the first data on the situation in Switzerland.
